**Methods/design:**

Using a phased cluster-randomized controlled trial design, we will evaluate the impact of the HITSystem on eight primary benchmarks in the 18-month long cascade of care for early infant diagnosis. Study sites are six government hospitals in Kenya matched on geographic region, resource level, and patient volume. Early infant diagnosis outcomes of mother-infant dyads (*n* = 120 per site) at intervention hospitals (*n* = 3) where the HITSystem is deployed at baseline will be compared to the matched control sites providing standard care. After allowing for sufficient time for enrollment and 18-month follow-up of dyads, the HITSystem will be deployed at the control sites in the end of Year 3. Primary outcomes are retention among mother-infant dyads, initiation of antiretroviral therapy among HIV-infected infants, and the proportion of services delivered within the optimal time window indicated by national and study guidelines. Satisfaction interviews with participants and providers will inform intervention improvements. Cost-effectiveness analyses will be conducted to inform the sustainability of the HITSystem. Hypothesized outcomes include significantly higher retention throughout the 18-month early infant diagnosis process, significantly more services provided on-time at intervention sites, and a potential savings to the healthcare system.

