##### Timely delivery of EID Services

For each of the 8 EID intervention points (Table 1), we will create an Optimal EID Care Index to measure whether the service was completed at all (1 point) or never completed (0 point) and whether it was completed on-time (1 point) or off-time (0 point). For each EID intervention point, each mother-infant dyad may receive either 0 point (never completed), 1 point (off-time completion), or 2 points (on-time completion). From these data, we will create an Optimal EID Care Index score for each dyad by summing across the 8 EID intervention point scores (range of 0–16 points). Dyads receiving a minimum score of 0 will have completed none of the 8 EID intervention points. Dyads receiving a maximum score of 16 will have completed all 8 points on-time. Scores between 0 and 16 will reflect some combination of completion and on-time completion.

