To assess the impact of the HITSystem on timely administration of eight critical EID interventions (Optimal EID Care Index), we will analyze data using multilevel modeling (Proc MIXED in the SAS System version 9.4) [24] to account for the nesting of time within dyad within hospital. This will increase the precision of treatment effect estimates by more correctly estimating standard errors (that are not correctly estimated when nesting is ignored) and indicate inferences about change over time by condition. We will include covariates that may be associated with EID completion (e.g., infant sex, distance from hospital, cell phone ownership) in addition to any pre-intervention differences identified across conditions and hospitals. Outcome variables of interest include an aggregate score and sub-scale scores (based on the Optimal EID Care Index), infant age at first PCR test, proportion re-tested by 9 months, and proportion re-tested by 18 months.

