#### Power and sample size

To be conservative, the sample size calculation for the analyses to determine intervention efficacy for retention and ART initiation is based on the smallest effect size obtained in our pilot work, 0.44 (range 0.44–1.98). Using Murray’s method to conduct power analysis for group-randomized trials, we accounted for the number of groups, participants in each group, and intraclass correction (ICC) estimated at 0.05 [25]. This calculation required *n* = 120 mother-infants dyads from each of the six participant hospitals for a total of 720 infants (360 from intervention hospitals and 360 from control hospitals). A sample of 720 infants is sufficient to detect with 80 % power, an effect size of 0.44 with an ICC range from 0.01 to 0.05. Due to multiple planned comparisons, a more conservative alpha level of 0.01 will adjust for possible inflated type I error. Given the EID volume and low refusal rates anticipated (<1 % in the pilot study), the required sample size for each hospital should be met within 12 months of enrollment.

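### Timely delivery is assessed with an Index that also credits late completion, so a difference in the Index need not mean that more services were delivered on time

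*Protocol article*

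**What the plan says.** The abstract (Methods/design) lists among the primary outcomes "the proportion of services delivered within the optimal time window indicated by national and study guidelines", and hypothesises "significantly more services provided on-time at intervention sites". The end of the Background section describes the same primary domain as efficiency: turn-around times and the ability to meet age- and time-specific targets.

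Under Timely delivery of EID Services, the Optimal EID Care Index is scored so that, for each of the eight points in Table 1, "each mother-infant dyad may receive either 0 point (never completed), 1 point (off-time completion), or 2 points (on-time completion". The total is formed by "summing across the 8 EID intervention point scores (range of 0–16 points". The section itself notes that "Scores between 0 and 16 will reflect some combination of completion and on-time completion".

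Statistical analyses then ties the timeliness question to this Index: "To assess the impact of the HITSystem on timely administration of eight critical EID interventions (Optimal EID Care Index". The model is a multilevel model with time nested in dyad and dyad in hospital. "Outcome variables of interest include an aggregate score and sub-scale scores (based on the Optimal EID Care Index", and the same list adds infant age at first PCR test and the proportions re-tested by 9 and by 18 months. The sub-scales are not defined, and the abstract's proportion of services within the window is not on the list.

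**The concern.** The stated hypothesis is about services on time. The score that carries the analysis also gives a point for a service delivered late. The null hypothesis of the aggregate score is therefore no difference in completion and timeliness combined, which is not the null of the stated hypothesis.

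The HITSystem is meant, among other things, to identify dyads who have dropped out and to trace them (Trial intervention). Success there can turn a service that would never have happened into one that happens late. That is a real benefit, but it is a retention benefit, and retention is a separate primary outcome. If the aggregate Index is read as the timeliness result, a retention effect could be reported a second time as better timeliness.

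**Working it through.** **Plan's own figure.** The article gives no power or error figure for the Index. The 80% power under Power and sample size is stated for retention and ART initiation, so there is nothing to reproduce on this point.

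**Algebra from the scoring rule.** For one service, let q be the proportion on time and l the proportion late. The expected score is 2q + l = (q + l) + q, that is, completed plus on time. Over eight services:

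mean Index = 8 × (2q + l) = 8 × (q + l) + 8 × q.

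This follows from the protocol's scoring alone. The rates below are assumptions, since the article gives none.

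| Case | q | l | Completed, 8(q + l) | On time, 8q | Index |
|---|---|---|---|---|---|
| Control | 0.40 | 0.20 | 4.8 | 3.2 | 8.0 |
| Late only | 0.40 | 0.40 | 6.4 | 3.2 | 9.6 |
| On time falls | 0.35 | 0.45 | 6.4 | 2.8 | 9.2 |

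In the second row the Index rises by 9.6 − 8.0 = 1.6 with no change in on-time delivery. In the third it rises by 9.2 − 8.0 = 1.2 while on-time services fall by 3.2 − 2.8 = 0.4 per dyad.

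**How often the test would reject.** From the article: three hospitals per arm, 120 dyads each, an ICC range of 0.01 to 0.05, and "a more conservative alpha level of 0.01 will adjust for possible inflated type I error". Assumed: the rates, a two-sided test, and a t-test on the six hospital means with 4 degrees of freedom, standing in for the multilevel model. Each setting used 2,000 simulated trials with hospital and dyad random effects. On-time delivery was equal in both arms and only late completion differed.

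- Simulation A used seven applicable points and ordered latent-normal scores. Late completion of 20% against 40% moves the Index by 7 × (0.40 − 0.20) = 1.4 points.
- Simulation B used all eight points. The mean Index difference came out at about 1.45 instead of 1.6, because the rates are set for an average hospital and dyad, and averaging over the random effects pulls the two arms slightly together.

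Rejection at alpha 0.01:

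| On time 40% in both arms; late, control v intervention | Index ICC | Index test | On-time count |
|---|---|---|---|
| A: 20% v 40% | roughly 0.01 to 0.05, three steps | 36%, 22%, 13% | about 1% |
| B: 20% v 20% | about 0.017 / 0.06 | 0.7% / 0.5% | 0.9% / 0.6% |
| B: 20% v 30% | about 0.017 / 0.06 | 6% / 2% | 0.9% / 0.7% |
| B: 20% v 40% | about 0.016 / 0.06 | 28% / 9% | 1.0% / 1.0% |

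The on-time count holds its nominal level throughout. The Index test exceeds it whenever late completion differs, by an amount that depends on the size of that difference and on the ICC.

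**Overlap with retention.** Under EID retention, incomplete care is defined by five items: DBS collection, notification of the mother, ART initiation, and re-testing at 9 and at 18 months. All five are among the eight Index points. OI prophylaxis, receipt of the sample at the laboratory and return of the PCR result are in the Index only. The overlap is five of eight steps.

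**The case against.** The strongest reply is that the aggregate Index is not the only timing analysis. The scoring rule consists of two separate binaries, completed and on time, and these are a natural pair of sub-scales. Age at first PCR test and the two re-test proportions are listed as outcomes. Time to ART, result turn-around time and time to notification are defined under Primary EID outcomes. Each of the eight outcomes will also be compared descriptively by arm. A purely late gain should show in several of these. This stands in part: a reader might infer that the plan has no way to see on-time delivery, and that would be wrong. But the sub-scales are undefined and could equally be per-service 0-2 scores with the same property. The other measures concern particular steps, and none is designated as the test of on-time delivery across the benchmarks.

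A second reply is that sub-scale definitions belong in an analysis plan that is not shown. That would answer a charge of omission. Here the article states both the outcome and the score used to assess it, and the two differ.

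A third is that the stress case is extreme: late completion doubles at every point with no on-time gain at all. This is fair. Alerts timed from the date of birth, real-time results and laboratory alerts act on timing, and the Background section describes much of the existing problem as lateness, where the expected shift is from late to on time. Steps 3 to 6 in Table 1 have windows that run from an earlier step, so a recovered dyad may also gain services that are truly on time.

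Finally, ranking never, late and on time is a defensible ordered score that keeps lost dyads in the analysis. That supports the Index as a measure of overall care, though not as evidence for an on-time claim.

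**Conclusion.** The mismatch is real and follows from the protocol's own scoring: the aggregate Index can differ between arms when on-time delivery is the same or worse. Its practical size rests on assumed rates and on the hospital-mean t-test. Near the planning ICC of 0.05 and at alpha 0.01, the late-only stress case leads to rejection in about one trial in eight to eleven. At lower ICCs it is roughly three in ten or somewhat more.

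Two stronger readings are not supported. One is that the test will reject whenever only late services are added. It can reject, but with six hospitals it usually would not in the scenarios near the planning values. The other is that the Index simply counts retention twice. The overlap is partial, and retention is a single complete/incomplete outcome for each dyad. Nor does the article say that an aggregate difference alone will be reported as more services on time. The defect is that nothing in it prevents that reading, and no outcome is named that would settle the question.

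**What to change.** In Statistical analyses, name as the outcome that tests the on-time hypothesis the number or proportion, per dyad, of applicable benchmarks completed within the window, with a service never completed counted as not on time. The word applicable matters because ART initiation concerns only infected infants and re-testing only uninfected ones. Use the same multilevel model. Define the sub-scale scores. Keep the 0/1/2 Index as a secondary summary of overall care, and state that it does not by itself support a claim of more services on time.

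The cost is a change of wording. The on-time indicator is already recorded to build the Index, and the Trial status section reports that no analyses had been conducted. The drawback is that an on-time count is less sensitive if the benefit is mainly late completion, but the retention outcome largely captures that benefit.

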#### Power and sample size

To be conservative, the sample size calculation for the analyses to determine intervention efficacy for retention and ART initiation is based on the smallest effect size obtained in our pilot work, 0.44 (range 0.44–1.98). Using Murray’s method to conduct power analysis for group-randomized trials, we accounted for the number of groups, participants in each group, and intraclass correction (ICC) estimated at 0.05 [25]. This calculation required *n* = 120 mother-infants dyads from each of the six participant hospitals for a total of 720 infants (360 from intervention hospitals and 360 from control hospitals). A sample of 720 infants is sufficient to detect with 80 % power, an effect size of 0.44 with an ICC range from 0.01 to 0.05. Due to multiple planned comparisons, a more conservative alpha level of 0.01 will adjust for possible inflated type I error. Given the EID volume and low refusal rates anticipated (<1 % in the pilot study), the required sample size for each hospital should be met within 12 months of enrollment.

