## Methods/design

### Trial design

This is a 5-year phased cluster-randomized, controlled trial design to rigorously evaluate the impact of the HITSystem in Kenya. Study sites are six government hospitals in Kenya matched on geographic region, resource level, and patient volume to produce three-matched pairs. One hospital in each pair was randomly assigned to either the intervention (HITSystem) or control group (standard of care) condition; resulting in three interventions and three control study sites. We anticipate a 12-month window to complete enrollment of *n* = 120 mother-infant dyads per hospital, followed by an 18-month follow-up period (until end of Year 3). In Year 4 the HITSystem will cross over to initial control sites whose standard of care data from the 12 months prior will serve as a comparison for analyses.

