##### Time to ART initiation

In addition to calculating the proportion of HIV-infected infants who are initiated on ART, we will calculate the number of days between the date that the mother was notified of her infant’s HIV-positive status and the date the infant was initiated on ART.

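### The 80% power claim covers ART initiation, but the calculation counts all 720 HIV-exposed infants although that outcome exists only for HIV-infected ones

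*Protocol article*

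**What the plan says.** The section on power and sample size of the protocol article presents a single calculation for two outcomes: "the sample size calculation for the analyses to determine intervention efficacy for retention and ART initiation is based on the smallest effect size". The inputs are "the smallest effect size obtained in our pilot work, 0.44", an ICC estimated at 0.05, and 120 mother-infant dyads at each of six hospitals, "for a total of 720 infants (360 from intervention hospitals and 360 from control hospitals"). The design section gives the clusters: "resulting in three interventions and three control study sites". The result is put this way: "A sample of 720 infants is sufficient to detect with 80 % power", "an effect size of 0.44 with an ICC range from 0.01 to 0.05". The same section adopts alpha 0.01 because of multiple comparisons. It does not say whether the power figure was computed at 0.01 or 0.05, or whether the test is two-sided.

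The abstract lists among the primary outcomes "initiation of antiretroviral therapy among HIV-infected infants". The section on time to ART initiation uses the same denominator, "calculating the proportion of HIV-infected infants who are initiated on ART". Eligibility, by contrast, covers HIV-infected mothers and their exposed infants whatever the infant's own status. The article states neither an expected number or share of infected infants nor a separate calculation for them.

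**The concern.** The denominator used for power is not the denominator of the outcome. Every dyad contributes to retention, but only infants found to be infected can contribute to the proportion started on ART. The effective cluster size for that outcome is 120 multiplied by the share infected, and the calculation leaves out this factor.

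Starting infected infants on treatment promptly is the purpose that the background section gives for early infant diagnosis. If a comparison of ART initiation is non-significant and is read against a published 80% power, a reader could take it as evidence of no effect when the design had little chance of detecting the stated effect.

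**Working it through.** **Inputs from the protocol.** Effect size d = 0.44; three hospitals per arm; 120 dyads per hospital; ICC 0.01 to 0.05; alpha 0.01 adopted for the analyses, with 0.05 also tried because the alpha behind the 80% is not stated. **Assumed:** two-sided tests, and a share infected, p, of 3% to 15%, because the protocol gives none.

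**Formulas.** With m infants per hospital contributing to the outcome:
- design effect: DEFF = 1 + (m − 1) × ICC
- standard error in SD units: SE = √(2 × DEFF / (3m))
- noncentrality: 0.44 / SE
- power from a noncentral t on 4 df (six hospitals less two arms) or from the normal approximation. The normal figures are generous because they ignore how few hospitals there are.

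**Step 1: the plan's own figure, m = 120.**
- ICC 0.01: DEFF = 2.19, SE = 0.110, noncentrality 3.99. Power at alpha 0.05 is 84% (t) or 98% (normal); at 0.01 it is 44% or 92%.
- ICC 0.05: DEFF = 6.95, SE = 0.197, noncentrality 2.24. Power at alpha 0.05 is 40% (t) or 61% (normal); at 0.01 it is 13% or 37%.

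So 80% is reached near ICC 0.01 but is not reproduced at 0.05, before any infant is excluded.

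**Step 2: infected infants needed, ignoring clustering.** n per arm = 2 × (z for alpha + z for power)² / 0.44².
- Alpha 0.05: 2 × (1.960 + 0.842)² / 0.1936 = 81.1, so 82 per arm; 82/360 = 23%.
- Alpha 0.01: 2 × (2.576 + 0.842)² / 0.1936 = 120.7, so 121 per arm; 121/360 = 34%.

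With ICC 0.01 (normal) the needs rise to about 112 per arm (31%) and 201 per arm (56%). At ICC 0.05 no share suffices: however large m is, SE cannot fall below √(2 × 0.05 / 3) = 0.183, so the noncentrality stays below 2.41 and power at alpha 0.05 stays below about 67%, even on the normal approximation.

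**Step 3: power for ART initiation, m = 120p.** Example at p = 5%, ICC 0.05: m = 6, DEFF = 1.25, SE = √(2.5/18) = 0.373, noncentrality 1.18, power 15% (t, alpha 0.05). Each cell gives ICC 0.01 / ICC 0.05.

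| Share infected | Infected per arm | t, α 0.05 | normal, α 0.05 | t, α 0.01 | normal, α 0.01 |
|---|---|---|---|---|---|
| 3% | 10.8 | 12% / 12% | 17% / 16% | 3% / 3% | 6% / 5% |
| 5% | 18 | 17% / 15% | 25% / 22% | 4% / 4% | 10% / 8% |
| 10% | 36 | 28% / 21% | 43% / 32% | 8% / 6% | 21% / 14% |
| 15% | 54 | 37% / 25% | 56% / 39% | 11% / 7% | 32% / 19% |
| all dyads | 360 | 84% / 40% | 98% / 61% | 44% / 13% | 92% / 37% |

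The last row isolates the denominator error. At ICC 0.01 (t, alpha 0.05) it takes power from 84% to 12-37%. At ICC 0.05 it takes power from 40% to 12-25%; the drop from 80% to 40% has another cause.

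**Step 4: does the scale of the effect matter?** If 0.44 is an arcsine difference between proportions, starting from an illustrative 33% (the background section puts ART initiation in Kenya below one-third), the other proportion is 55%. Unclustered normal power at alpha 0.05 with 18, 36 and 54 infants per arm is then 25%, 46% and 62%. The standardised-mean version gives 26%, 46% and 63%. It makes little difference.

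**The case against.** The best reply is that 0.44 was chosen as the smallest pilot effect, in a range up to 1.98, and that the effect on ART initiation may be far larger. That stands as a limit on the finding. At 1.98 with 5% infected, power (t on 4 df) is 97-99% at alpha 0.05 and 71-79% at alpha 0.01. A reader might infer that the trial cannot detect any effect on ART initiation; the protocol does not support that, since it does not say which pilot effect belongs to which outcome. But the 80% is claimed at 0.44, and there it fails.

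A second reply is that ART initiation is also one component of the composite retention outcome, to which every dyad contributes. That is true and softens the consequence. However, the power section names ART initiation beside retention, and the abstract lists it as a primary outcome in its own right.

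Third, the infection rate is an assumption. The protocol gives no figure, so it would be wrong to state as fact that infected infants are a small fraction of the 720. Step 2 needs no such assumption: it gives the share that would have to be infected. At an assumed 20%, power at alpha 0.05 is still at most 75% without clustering, and 28-66% across the ICC range and both methods.

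Finally, a reader might attribute the whole gap from 80% to the denominator. Step 1 shows that this is not so at ICC 0.05.

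**Conclusion.** The concern holds for the claim as written: 80% power for ART initiation at effect size 0.44 does not follow from 720 HIV-exposed infants. Unless at least 23% of enrolled infants are infected (34% at alpha 0.01), the figure is out of reach even with no clustering. For an assumed 3-15% infected, power across ICC 0.01-0.05 is 12-37% (t) or 16-56% (normal) at alpha 0.05, and 3-11% or 5-32% at alpha 0.01. These figures rest on two-sided tests, equal cluster sizes and the assumed infection range. The inability to reproduce 80% for the full sample at ICC 0.05 is a separate defect that also touches retention. It should neither be counted as part of this one nor be hidden by correcting this one.

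**What to change.** Remove ART initiation from the 80% power statement. State the expected number of infected infants per hospital; the 12-month retrospective registry review, which the protocol reports as already conducted at each hospital, should supply it. Then do one of two things:
- Give the detectable effect for ART initiation at the alpha that will be used. For scale, at an assumed 5% infected it is about 1.27 to 1.39 at alpha 0.05 and 1.89 to 2.07 at alpha 0.01, from SE × (t for alpha + t for 80% power) on 4 df: 0.342 or 0.373 multiplied by (2.776 + 0.941) or (4.604 + 0.941).
- Or report ART initiation as an estimate with a confidence interval, and note that a non-significant result is not evidence of no effect.

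In either case, do not restate 80% for retention at ICC 0.05 without recomputing it. The change is to wording plus one short calculation. It needs no new data collection, and the article reports that no analyses had been done. The cost is that one published power claim becomes less favourable.

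### The stated 80% power for an effect size of 0.44 is not reached at the planning ICC of 0.05: with 3 versus 3 hospitals it is about 40% at alpha 0.05 and 13% at alpha 0.01

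*Protocol article*

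**What the plan says.** The section on power and sample size bases the calculation, for retention and ART initiation, on the "smallest effect size obtained in our pilot work, 0.44 (range 0.44–1.98"), chosen as the conservative value. It names Murray's method for group-randomized trials and says that "we accounted for the number of groups, participants in each group" and an "intraclass correction (ICC) estimated at 0.05". The result is 120 "mother-infants dyads from each of the six participant hospitals for a total of 720 infants", split equally between the arms. The claim itself is that "720 infants is sufficient to detect with 80 % power, an effect size of 0.44 with an ICC range from 0.01 to 0.05".

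The following sentence says that, because several comparisons are planned, "a more conservative alpha level of 0.01 will adjust for possible inflated type I error". The trial design section describes three matched pairs of hospitals, "resulting in three interventions and three control study sites".

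The article does not give the sidedness, the degrees of freedom or the alpha behind the 80%.

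**The concern.** With only six randomised hospitals, the precision of the arm comparison is set mainly by variation between hospitals. At ICC 0.05 and 120 dyads per hospital, the variance is inflated about sevenfold, and the test has few degrees of freedom. An effect of 0.44 then looks too small to be found with 80% probability, the more so at alpha 0.01.

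This is the only quantitative justification of the sample size in the article. If it is wrong, a non-significant result could be read as evidence from an adequately powered trial that the system does not improve retention, when the trial had well under an even chance of detecting the effect it planned for.

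**Working it through.** **Inputs from the article.** Effect size d = 0.44; hospitals per arm g = 3; dyads per hospital m = 120; ICC 0.01 to 0.05, planning value 0.05; alpha 0.01 for the planned comparisons.

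**Assumptions.** The effect size is a difference in standard deviation units. The pilot range extends to 1.98, which rules out a correlation or a risk difference, since neither can exceed 1. The test is two-sided. The arm effect has 2(g − 1) = 4 degrees of freedom. Alpha 0.05 is shown beside 0.01 because the alpha behind the 80% is unknown.

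**Formulas.** Design effect = 1 + (m − 1) × ICC. SE(d) = √(2 × design effect / (m × g)). Noncentrality = d / SE. Power comes from the noncentral t on 4 df, with critical values 2.776 (alpha 0.05) and 4.604 (alpha 0.01).

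**Attempt to reproduce the stated figure at ICC 0.05.**
- Design effect = 1 + 119 × 0.05 = 6.95.
- SE = √(2 × 6.95 / 360) = 0.1965.
- Noncentrality = 0.44 / 0.1965 = 2.24.
- Power on 4 df: 40.2% at alpha 0.05 and 12.9% at alpha 0.01.

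The 80% is not reproduced. More lenient variants at the same ICC also fall short:

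| Test at ICC 0.05 | alpha 0.05 | alpha 0.01 |
|---|---|---|
| Two-sided t, 4 df | 40.2% | 12.9% |
| One-sided t, 4 df | 58.1% | 21.9% |
| Two-sided large-sample | 61.0% | 36.8% |
| One-sided large-sample | 72.4% | 46.5% |

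**Across the ICC range (two-sided, 4 df).** For 80% power the noncentrality must be about 3.76 at alpha 0.05 and 5.88 at alpha 0.01. The detectable effect is that value times the SE.

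| ICC | Design effect | SE | Power, alpha 0.05 | Power, alpha 0.01 | Detectable effect, 0.05 / 0.01 |
|---|---|---|---|---|---|
| 0.01 | 2.19 | 0.1103 | 84% | 44% | 0.41 / 0.65 |
| 0.02 | 3.38 | 0.1370 | 68% | 28% | 0.52 / 0.81 |
| 0.05 | 6.95 | 0.1965 | 40% | 13% | 0.74 / 1.16 |

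On 4 df at alpha 0.05, power stays at 80% only up to an ICC of about 0.012. At alpha 0.01 it needs an ICC of essentially zero (80.3% at ICC 0). A large-sample test at ICC 0.01 gives 98% and 92%, so the shortfall at that end depends on using cluster-level degrees of freedom; the shortfall at ICC 0.05 does not.

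**Could more dyads per hospital help?** With unlimited dyads at ICC 0.05, power on 4 df is capped at 45% (alpha 0.05) and 15% (alpha 0.01). The constraint is the number of hospitals.

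**The case against.** **The 80% may have been computed at alpha 0.05.** The 0.01 level comes in a separate sentence and is tied to multiple comparisons. This is fair. On that reading the 13% shows a mismatch between the power claim and the testing level, and the 40% is what contradicts the calculation. At ICC 0.01 and alpha 0.05 the stated figure is met, but the sentence extends it to 0.05, which is also the planning value.

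**Matching and adjustment could reduce variation between hospitals.** The hospitals are matched, a year of pre-study outcomes is collected, and covariate adjustment is planned. This stands as a qualification. If 75% of the between-hospital variance were removed with 4 df kept, power at ICC 0.05 would be 80% at alpha 0.05 and 40% at alpha 0.01. But the article quantifies no reduction. A paired analysis would also leave only 2 df: power is then 26% and 6% if matching removes nothing, 38% and 9% if it removes half, and 68% and 21% if it removes 90%. The lowest of these should not be quoted alone as the power of a paired analysis.

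**The effect-size scale is unnamed.** If 0.44 were half a standardised difference (d = 0.88), power at ICC 0.05 would be 91% at alpha 0.05 and 55% at alpha 0.01. Nothing in the article supports that reading.

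**True effects may be larger.** The pilot range runs to 1.98, and for d = 1.2 at ICC 0.05 power on 4 df is 99% and 83%. The trial may therefore be informative, but the claim was made for 0.44.

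**Two stronger readings are not supported.** A reader might infer that power at alpha 0.01 is at most 13% to 44%. That ceiling depends on 4 df, which is the sound choice but is not stated in the article. A reader might also infer that a flat 0.01 is itself an error, because the abstract lists "eight primary benchmarks in the 18-month long cascade of care" and eight independent tests at 0.01 give 1 − 0.99⁸ = 7.7% familywise error. The article promises no 5% familywise rate and does not define the family, so this is not a contradiction.

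**Conclusion.** The power statement is wrong as written. None of the usual tests tried on the article's own inputs, one- or two-sided and with or without small-cluster degrees of freedom, reaches 80% at ICC 0.05; the best, a one-sided large-sample test at alpha 0.05, gives 72%. On the sound basis, the claim overstates power about twofold at alpha 0.05 (80 / 40) and about sixfold at alpha 0.01 (80 / 13).

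The conclusion at ICC 0.05 rests on reading 0.44 as a standardised difference and on no unstated variance reduction. At the low end of the ICC range the claim holds at alpha 0.05; at alpha 0.01 it fails there only if cluster-level degrees of freedom are used. The finding concerns the stated power and does not show that the design or the testing rule must change.

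**What to change.** Replace the power sentence with a short table for six hospitals of 120 dyads, giving power for 0.44 and the effect detectable with 80% power at ICC 0.01, 0.02 and 0.05. Compute it with cluster-level degrees of freedom at the alpha that will be used for the tests. State the effect-size scale, the sidedness, the degrees of freedom and any variance reduction assumed from matching or covariates, with its basis. The figures above can serve if the two-sided, 4-df, no-reduction assumptions are the intended ones.

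Add one sentence saying that a null result is inconclusive for effects below the recomputed detectable size.

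The cost is wording and a less favourable stated figure. No dyads or hospitals are added, and neither alpha nor the handling of multiple comparisons needs to change. The trial status section reports that no analyses had been done, so at that stage the correction could be made without knowledge of results.
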